### Sample size

For a pilot RCT with continuous outcomes, the recommended total sample size is 70, with 35 in each study arm with relative change in outcome variables within 95% confidence interval [41].

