### Biomarkers analyses and statistical analyses plan

In the analyses of the biomarkers, aliquoted plasma will be used to measure the cytokines and metabolic profiles of the research participants using single-analyte enzyme-linked immunosorbent assay (ELISA). Using targeted approach, selected RNA targets, which may include messenger RNA and micro-RNA, for a subset of the subject will be analysed based on the data obtained from the cytokines and metabolic profiles. Whole bloods aliquoted on Trucount tubes are stained with a series of fluorescence-conjugated antibodies marking the surface receptors of immune cell. Using flow cytometer, part of the phenotyping includes classical markers of senescence, Cluster of differentiation 57 (CD57) and Killer-cell lectin like receptor G1 (KLRG1), exhaustion of T cells, Programmed cell death protein 1 (PD1) and potentially identification of subpopulations of B cells and myeloid cells with a focus on the pro-inflammatory cells. The extent of DNA damage repair will be assessed by flow cytometry as well. Other immuno-assays aiming at identifying markers or predictors of immune status to examine the effects of the interventions may be applied with the bio-banked samples.

In the data analyses procedures, statistical significance level will be set at .05 for all descriptive and statistical analyses. All analyses will be performed using the SPSS. Based on the initial condition assignment and using the last observation carried forward (LOCF) method, intention-to-treat analyses will be conducted. Preliminary analyses will be performed next to assess the influence of demographic factors that (age, gender, education level, marital status, etc.). Where necessary, these variables will be included as covariates or control variables in the analyses. As some attrition is expected between interviews, prior to data analysis, comparisons will be made of retained and non-retained participants, to determine whether there are any systematic differences.

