If there are chance imbalances in baseline participants’ characteristics, they will be entered as covariates in the analyses. Repeated Measure Analysis of Variance (ANOVA) will be used to examine the difference of the outcome between the active treatment group and waitlist control group over the 3 time points [42]. If there are imbalances in baseline participants’ characteristics, those variables will be included as covariates in the analyses. Additionally, dependent t-test will be employed to analyse the changes in scores within the active treatment group across the 3 time-points.

Ratios of selected biomarkers will be taken between cortisol, IL-6, CRP and DHEA-S. Additionally, fold changes and percentage changes would be performed. In the case of significant difference between the baseline measurements of prognostic demographic variables, multivariate regression will be performed when examining the differences between the means of the biomarkers for the two study arms. Correlation and/or heatmap analyses will be carried out to examine the relationships between the biomarker levels. On the aggregate biomarker level, principal component analyses (PCA) will be performed to examine the overall effect of the treatment. Mediational analyses employing bootstrapping technique will be employed to explore the mediating variables between the psychometric outcomes and biomarker levels.

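### Biomarker comparison: no log scale or baseline-biomarker covariate is named, and the fold and percentage changes that are named mislead within an arm and would cost power if used to compare arms

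*Protocol article*

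**What the plan says.** The section on biomarker and statistical analyses names four things for the markers.

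- Ratios: "Ratios of selected biomarkers will be taken between cortisol, IL-6, CRP and DHEA-S".
- Change measures: "Additionally, fold changes and percentage changes would be performed".
- A comparison of arm means, with a regression whose trigger is "In the case of significant difference between the baseline measurements of prognostic demographic variables". In that case "multivariate regression will be performed when examining the differences between the means of the biomarkers for the two study arms".
- Correlation, heatmap, principal component and mediation analyses, which are not at issue here.

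The same section names repeated-measures ANOVA over the three time points as the general between-arm model, and lets imbalanced baseline characteristics enter as covariates. It sets the test level: "statistical significance level will be set at .05 for all descriptive and statistical analyses". It mentions no transformation and does not name the baseline level of a marker as a covariate. The Sample size section gives 35 per arm, with no effect size, standard deviation or power.

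**The concern.** Percentage and fold changes divide by a baseline that itself varies. Halving counts as -50% and doubling as +100%, so a few participants with low baselines can dominate an arm's mean. A ratio of two markers has the same asymmetry, and its mean depends on which marker is the numerator. The log of a ratio only changes sign when the ratio is inverted.

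The regression trigger looks at demographic variables, whereas the strongest available predictor of a follow-up marker level is normally its own baseline, which is already collected.

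The article presents the markers as objective support for self-reported mental health in a trial with a waitlist control. A summary that drifts upwards, or a comparison that misses a real fall, weakens that support.

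**Working it through.** **Inputs from the document.** 35 per arm ("the recommended total sample size is 70, with 35 in each study arm") and alpha 0.05, taken as two-sided because sidedness is not stated.

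**The plan's own figure.** The total of 70 cannot be rebuilt, because its only justification is a pilot-trial recommendation "with relative change in outcome variables within 95% confidence interval". For scale, 35 per arm detects a standardised difference of (1.960 + 0.842) × √(2/35) = 0.67 at 80% power.

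**Assumptions.** The marker is log-normal with log-SD s at each visit and baseline-to-follow-up correlation r on the log scale. The document gives neither s nor r, so a range is shown.

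**Step 1: drift with no true change.** The log fold change has mean 0 and variance 2s²(1−r), so the mean fold change is exp(s²(1−r)).

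- s = 0.3, r = 0.8: exp(0.018) − 1 = +1.8%
- s = 0.5, r = 0.5: exp(0.125) − 1 = +13.3%
- s = 0.8, r = 0.5: exp(0.320) − 1 = +37.7%
- s = 1.0, r = 0.5: exp(0.500) − 1 = +64.9%

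A true 30% fall has expected percentage change 0.7 × exp(s²(1−r)) − 1. At r = 0.5 this is −3.6% for s = 0.8 and +15.4% for s = 1.0, the latter with the sign reversed.

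**Step 2: does the drift bias the randomised comparison?** No. It is the same in both arms. In 3,000 simulated null trials per scenario, type I error was 0.037 to 0.056 across all methods and scenarios.

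**Step 3: power at 35 per arm.** There were 4,000 simulated trials per scenario. The true ratio was set at exp(−2.802 × s × √((1−r²) × 2/35)), so that log-scale ANCOVA has about 80% power. Percentage and fold change give the same test, since one is a linear function of the other. Losses, in points against log ANCOVA, are in brackets.

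| s | r | True ratio | Log ANCOVA | Percentage/fold change | Untransformed follow-up means | Untransformed change |
|---|---|---|---|---|---|---|
| 0.3 | 0.5 | 0.84 | 79.0% | 65.6% (13.4) | 65.8% (13.2) | 60.4% (18.6) |
| 0.3 | 0.7 | 0.87 | 77.8% | 69.6% (8.2) | 49.0% (28.8) | 65.1% (12.7) |
| 0.5 | 0.5 | 0.75 | 78.4% | 63.2% (15.2) | 61.3% (17.1) | 53.6% (24.8) |
| 0.5 | 0.7 | 0.79 | 76.3% | 67.6% (8.7) | 45.5% (30.8) | 56.0% (20.3) |
| 0.8 | 0.5 | 0.63 | 77.4% | 53.6% (23.8) | 54.6% (22.8) | 39.2% (38.2) |
| 0.8 | 0.7 | 0.68 | 79.9% | 64.0% (15.9) | 40.6% (39.3) | 45.0% (34.9) |
| 1.0 | 0.5 | 0.56 | 78.2% | 48.2% (30.0) | 46.7% (31.5) | 32.4% (45.8) |
| 1.0 | 0.7 | 0.62 | 77.5% | 59.5% (18.0) | 35.4% (42.1) | 34.0% (43.5) |

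The simulation standard error is at most √(0.25/4000) = 0.8 points. Untransformed change equals the group-by-time test of a repeated-measures ANOVA with two time points, so it is a proxy for the planned three-point model. Dropout and last-observation-carried-forward were not simulated.

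**Step 4: which part of the remedy does the work?** Both parts do. Log change without the baseline covariate still loses 6 to 12 points. ANCOVA on untransformed values loses 3 to 8 points at s = 0.3 to 0.5 and 16 to 26 at s = 0.8 to 1.0.

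**The case against.** The best defence is that the text commits to less than one might read into it.

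- The article never says that marker values stay untransformed. That is inferred from silence, and a separate analysis plan could supply a log scale. This stands.
- Fold and percentage changes are listed as an addition, next to descriptive analyses, and are not declared the tested between-arm outcome. They may already be meant for display. This stands, so the power figures apply only if they are used to compare arms.
- A reader might infer that baseline marker values go unused. The documents do not support that. Baseline is one of the three time points in the repeated-measures ANOVA, and change measures use it too. Imbalanced baseline characteristics may also become covariates without a significance condition; that condition belongs to the biomarker regression alone. What remains is that the baseline marker level is not named as a covariate.
- A reader might infer that the upward drift could create a false treatment effect. It cannot, because it cancels between randomised arms. The dependent t-tests within the active group are planned for scores, and a paired test on concentrations would not carry the drift either.
- The markers are supporting evidence in a trial sized as a pilot, with no power claim for them. This stands and limits the weight of the point.

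The defence does not make the named measures sound. Log-scale ANCOVA had the highest power in every scenario, including against the proxy for the repeated-measures ANOVA.

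**Conclusion.** The point holds in a limited form. The article names measures that behave poorly for positive, right-skewed markers and ties the biomarker regression to demographic differences, while naming neither a log scale nor the baseline marker level as a covariate.

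Two consequences follow. Within an arm, the mean percentage or fold change overstates a rise or hides a fall, by an amount that is small for stable markers and large for variable ones. Between arms, the test stays valid but is inefficient if it uses these measures or untransformed values. The loss for percentage change is modest at log-SD 0.3 to 0.5 and substantial at 0.8 to 1.0. For untransformed follow-up means it is about the same as for percentage change at correlation 0.5, and clearly larger at 0.7.

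A flat statement that the planned analysis has much less power would go too far, since it depends on variability that the document does not give. The sizes rest on log-normality, equal spread at both visits and one follow-up compared with baseline. The point is a cheap improvement for supporting outcomes; it does not touch a primary result.

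**What to change.** State one between-arm analysis for the markers: ANCOVA of the log follow-up value on arm, log baseline value of the same marker, and gender, which is the stratification factor. Analyse each marker ratio as a difference of logs in the same way. Report the adjusted geometric mean ratio, HT to waitlist, with 95% confidence interval at months 3 and 6. Keep fold and percentage changes as description only, without tests. Drop the significance test of demographic variables as the trigger for adjustment in the biomarker analysis.

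The cost is a few lines of plan text and one transformation, with no new data. One rule must be added: a fixed substitution or a censored model for values below the assay limit. Because the article reports data collection complete and analyses under way, the change should be dated, with a note of whether any biomarker comparison by arm had already been seen.

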### Protocol compliance and deviation/violation

A Note-to-file will be raised in the site investigator file and serious adverse events will be reported to the NUS-IRB.

## Discussion

This RCT study has been designed to test the effectiveness of HT in improving the mental, cognitive and physical health of the older adults. Studies have shown that contact with nature has been associated with positive mood and improved sleep quality [13] and HT which allows for engagement with nature has been suggested to mitigate stress and improve mood state [7]. This study will be conducted on a multi-racial Asian population to provide substantiation if HT can improve mental health, cognitive functioning or physical health. With the objective measures of biomarkers as collaborative evidence, the proposed study will make significant contributions, both to a theoretical understanding of mental and cognitive health and to providing needed information to the healthcare providers coping with an ageing population.

In addition, this study is evaluating not only quantitative data but also qualitative data via feedback questionnaire. This will provide information on the subjective experience of the participants, and to inform areas of improvement for future programs as ultimately our focus will be on the benefits to the individual and the opportunities to continue such a program beyond the duration of the project.

HT may offer a playful and enjoyable experience to the participants, thereby providing an intrinsic motivation and increasing compliance. Hence, older adults would be self-motivated to appreciate nature and be engaged in gardening even after the program ends. As a basic premise of this community-based initiative, we seek to build the capacity of the participants and empower them to take charge of their own health. This change in lifestyle will enhance their physical activity levels, and consequently increasing their health and ability to cope more effectively with the challenges faced in their daily life.

Community-based HT may provide an avenue for older individuals to socialize more and improve their mental health. After retirement, they are more likely to lead a sedentary lifestyle, with only 30% of them reaching the recommended level of leisure-time activity [43] and slightly more than half (58%) in Singapore were sedentary [44]. Especially for those who are living alone, they might experience loneliness due to a lack of social interaction, which could in turn increase their risk for mental health problems [45]. Participation in HT will help build a sense of social connectedness amongst the older individuals. It is noteworthy that the proposed intervention also includes some physical exercise and educational components aiming to motivate the participants to carry on gardening at home. These various components aim to be holistic in delivering its benefits to the participants, as well as to encourage participants to adopt it as a lifestyle change. In addition, different locations will be used to conduct the intervention. Although this may add to the heterogeneity of such interventions, it reflects that such interventions, which are contingent on its environmental aspects, need to be adjusted to the local and cultural context.

The program can be easily translated to older adults’ activities of daily living. Singapore, termed a “Garden City” has more than 350 parks which are close to homes for easy access [46]. Hence, urban parks are inexpensive resources readily available for the older adults to engage in walks and gardening activities. In addition, as part of the HT program, plants are given to participants to tend to at home, encouraging them to incorporate gardening as part of their daily routine.

Such community-based interventions supported by volunteers are important as they have the potential to be sustained. With its clinical implications, this initiative will guide future larger research trials and healthcare providers of the need to support cost-effective HT as a strategy to engage older adults in a more active and healthier lifestyle. In the context of the growing worldwide mental illness burden of disease, HT will go a long way in easing public healthcare, social and economic costs.

### Study progress

The study has completed data collection.

Intervention programme for the waitlist control and data analyses are currently ongoing. Data analyses are estimated to be completed in October 2016.

## Abbreviations

ANOVA: Analysis of Variance
BDNF: Brain-derived neurotrophic factor
CD57: Cluster of differentiation 57
CDR: Clinical Dementia Rating
CRP: C-reactive protein
CRP: C-reactive protein
DHEAS: Dehydroepiandrosterone Sulphate
DMSO: Dimethyl Sulfoxide
DNA/RNA: Deoxyribonucleic acid/Ribonucleic acid
ELISA: Enzyme-Linked Immunosorbent Assay
FBS: Fetal Bovine Serum
HT: Horticultural Therapy
IL-1β: Interleukin-1 beta
IL-6: Interleukin 6
KLRG1: Killer-cell Lectin like Receptor G1
MoCA: Montreal Cognitive Assessment
PBMC: Plasma and Peripheral Blood Mononuclear Cells
PBS: Phosphate-buffered Saline
PCA: Principal Component Analyses
PD1: Programmed Cell Death Protein 1
RAVLT: Rey Auditory-Verbal Learning Test
RCT: Randomized Controlled Trial
SAS: Zung Self-Rating Anxiety Scale
SDS: Zung Self-Rating Depression Scale
SPSS: Statistical Package for Social Sciences
SWLS: Satisfaction with Life Scale
